## Abstract

**Introduction:**

While clinicians commonly prescribe neuromodulators for the treatment of refractory or unexplained chronic cough, no trials have directly compared these treatments. Furthermore, although guidelines recommend non-pharmacological management involving physiotherapy and speech-language therapy, few trials have evaluated its effectiveness.

**Methods and analysis:**

FORTITUDE (*F*act*O*rial *R*andomized *T*r*I*al *T*o eval*U*ate neuromo*D*ulators and cough control th*E*rapy) is a 6-week, 2×2 factorial, randomised, open-label trial with an observational extension up to 1 year. The trial will include Canadian hospital sites enrolling 124 patients. Patients ≥18 years old with either refractory or unexplained chronic cough will undergo independent 1:1 randomisation to pharmacotherapy—either low-dose morphine (up to 5 mg two times per day) or pregabalin (up to 150 mg two times per day)—and concurrent cough control therapy (CCT) or no CCT. The CCT will consist of five virtual sessions delivered over 6 weeks by a trained physiotherapist or speech-language pathologist. Change from baseline in 24-hour cough frequency at 6 weeks represents the primary outcome. Secondary outcomes include change from baseline in awake, sleep and cough bout frequencies; cough severity on the McMaster Cough Severity Questionnaire and the 100-mm Visual Analogue Scale; and cough quality of life on the Leicester Cough Questionnaire at 6 weeks. We will analyse safety and tolerability at 6 weeks and explore potential interactions between neuromodulators and CCT. Follow-up in an observational extension of up to 12 months post-randomisation will assess long-term treatment patterns, adherence and safety in a real-world setting.

**Ethics and dissemination:**

Health Canada’s Pharmaceutical Drugs Directorate has provided approval to conduct this study. We have approval from the Hamilton Integrated Research Ethics Board of the Main Coordinating Site, with ethics pending at other participating sites. Results of the main trial and the observational extension will be published as manuscripts in peer-reviewed journals.

**Trial registration number:**

NCT07288528.

STRENGTHS AND LIMITATIONS OF THIS STUDYThe 2×2 factorial randomised design enables simultaneous evaluation of low-dose morphine versus pregabalin and cough control therapy (CCT) versus no CCT.The multicentre design across Canadian tertiary cough clinics enhances the generalisability of study findings to specialist clinical settings.The 6-week randomised treatment period is followed by an observational extension up to 1 year to assess long-term outcomes.The observational extension phase is not randomised, limiting the ability to make causal inferences about treatment groups beyond the 6-week randomised treatment period.The study is powered to detect the main effects of morphine versus pregabalin and CCT versus no CCT but is not powered to detect interactions between the two interventions.

## Introduction

### What is the problem to be addressed?

 Chronic cough lasting >8 weeks is a common health problem. In Canada, it affects 16% of adults aged >45 years, representing one of the highest prevalence rates globally.^1^ Although some patients respond to treatments addressing known causes of cough, approximately 26% have, despite optimal therapy, refractory or unexplained chronic cough (RCC/UCC).^2^

RCC/UCC can lead to substantial physical and psychosocial burden.^3^ Patients frequently experience chest pain, urinary incontinence, syncope, headaches, depression and sleep disturbance.^4
5^ Improving quality of life in these patients requires administration of effective therapies.

### Current management of RCC/UCC

In Canada and many countries globally, there remains no licensed treatments for RCC/UCC. Clinical practice guidelines^6
7^ therefore recommend behavioural cough suppression^8–10^ or off-label use of neuromodulators, including low-dose morphine,^11^ pregabalin^8^ or gabapentin.^12^

Two randomised trials have evaluated low-dose morphine given at 5–10 mg two times per day for 2–4 weeks in adults with RCC/UCC.^11
13^ The first trial in 27 patients found that, compared with placebo, morphine reduced cough severity by 2 points (95% CI 1.1 to 2.1) on a 10-point scale.^11^ The second trial in 22 known responders found that it improved 24-hour cough frequency by 71.8% and Cough Severity on the 100-mm Visual Analogue Scale (CS-VAS) by 27.2 mm compared with placebo.^13^ In both trials, patients generally tolerated morphine, and the most common side effects included constipation and drowsiness.^11
13^

Another neuromodulator, pregabalin, has shown benefit when combined with speech therapy. In a randomised trial of pregabalin (150 mg two times per day) plus speech therapy, the combination improved cough quality of life on the Leicester Cough Questionnaire (LCQ) by 3.5 points (95% CI 1.1 to 5.8) and the CS-VAS by 25.1 mm (95% CI 10.6 to 39.6 mm) compared with speech therapy alone.^8^ Treatment discontinuation occurred in 5% of patients due to drowsiness, nausea or weight gain.

Non-pharmacological interventions that combine education, cough suppression and behavioural modification have also shown benefit.^8–10
14^ In one randomised trial of 87 patients, speech pathology improved cough scores by 2.8 points (95% CI 1.3 to 4.0) on a 5-point scale compared with placebo.^9^ Another randomised trial of 75 patients evaluating physiotherapy with a speech and language therapy intervention (PSALTI) found that, compared with healthy lifestyle advice, PSALTI reduced cough frequency by 41% (95% CI 36% to 95%) and improved LCQ scores by 1.53 points (95% CI 0.21 to 2.85), with effects sustained up to 3 months.^10^ Together, these trials informed a conditional recommendation in favour of non-pharmacological interventions.^6^

### Gaps in the literature

Although current evidence supports the individual efficacy of low-dose morphine^11
13^ and pregabalin,^8^ no head-to-head trials have compared these treatments. The routine use of these agents highlights the need for a large randomised trial directly comparing their benefits and harms.

Furthermore, while guidelines recommend non-pharmacological interventions, randomised trial evidence remains limited to two small studies, with uncertainty regarding durability beyond 3 months,^10^ the specific intervention components that drive benefit, and the factors influencing scalability and broader implementation. This highlights the need for a rigorous evaluation of the effectiveness of a scalable virtual intervention, as well as its fidelity and implementation considerations.

### Why is this trial needed now?

Our trial is the first to evaluate two commonly prescribed neuromodulators—low-dose morphine and pregabalin—and a virtual non-pharmacological intervention called ‘cough control therapy’ (CCT).

We selected low-dose morphine based on evidence from two trials^11
13^ demonstrating cough improvements with doses between 5 and 10 mg two times per day. Although guidelines recommend both pregabalin and gabapentin,^6^ we selected pregabalin due to its more predictable pharmacokinetics and two times per day dosing,^15^ which may improve tolerability and adherence^16^ compared with gabapentin’s three times daily dosing.

Building on work from other groups^8
9
14^ and our own,^17
18^ we developed a structured CCT programme that can be delivered virtually. In a small observational cohort study of patients with RCC/UCC, our group demonstrated the feasibility of virtual CCT and observed a 59.3% reduction in 24-hour cough frequency following the intervention.^18^ We now propose to evaluate virtual CCT in a randomised trial alongside neuromodulators to clarify its independent and additive effects, and assess its acceptability, the components that drive benefit, intervention fidelity and implementation considerations.

## Objectives

The co-primary objectives of FORTITUDE (*F*act*O*rial *R*andomized *T*r*I*al *T*o eval*U*ate neuromo*D*ulators and cough control th*E*rapy) are to compare the effectiveness of (1) low-dose morphine versus pregabalin and (2) virtual CCT versus no CCT in adults with RCC/UCC. Secondary and exploratory objectives include assessment of the safety and tolerability of neuromodulators and CCT, exploration of potential interactions and evaluation of treatment adherence.

## Methods

### Patient and public involvement

Patient partners were involved in the design of the trial and will be involved in the interpretation and reporting of the trial results.

### Trial design

FORTITUDE is a multicentre, superiority, 2×2 factorial, randomised, open-label trial in adults with RCC/UCC (figure 1). Participants will undergo independent 1:1 randomisation to pharmacotherapy (low-dose morphine vs pregabalin) and CCT (CCT vs no CCT), generating four treatment combinations. Primary outcome assessment will occur at 6 weeks.

**Figure 1 F1:**
[figure not shown]
FORTITUDE study design. BID, two times per day; CS-VAS, Cough Severity Visual Analogue Scale; EQ-5D-5L, EuroQol-5 Dimensions-5 Instrument; FORTITUDE, *F*act*O*rial *R*andomized *T*r*I*al *T*o eval*U*ate neuromo*D*ulators and cough control th*E*rapy; LCQ, Leicester Cough Questionnaire; MCSQ, McMaster Cough Severity Questionnaire; PGIC, Patient Global Impression of Change Instrument.

Following the 6-week randomised period, participants will enter a 1-year observational extension with assessments at 6 and 12 months. Participants will not be required to remain on their randomised treatment, allowing us to examine real-world long-term effectiveness, treatment trajectories, tolerability and CCT uptake.

This trial will adhere to the 2025 Consolidated Standards of Reporting Trials (CONSORT),^19^ the Factorial Randomized Trials Extension^20^ and the 2025 Standard Protocol Items: Recommendations for Interventional Trials (SPIRIT) guidelines.^21^ The trial is registered on ClinicalTrials.gov (NCT07288528). Online supplemental files 1–3 include the Trial Structured Summary, the completed 2025 SPIRIT checklist and the Informed Consent Form. The estimated trial period is September 2026 to September 2029.

### Study setting

FORTITUDE will include five Canadian academic hospital clinics providing secondary or tertiary care to patients with RCC/UCC.

### Screening and informed consent

The study team will approach patients consecutively. Interested patients will receive a study information letter and consent form. Consent discussions may occur in person or by telephone. A research coordinator will obtain written informed consent at an in-person visit.

### Eligibility criteria

Eligible patients will include adults (≥18 years old) with either: (1) RCC, defined as having one or more identifiable causes of cough (asthma, upper airway disease and/or gastro-esophageal reflux disease), but with previous trials of treatment targeting the underlying condition leading to no cough resolution; or (2) UCC, defined as having a cough lasting >8 weeks with (a) a normal chest X-ray/CT in the last 5 years and since the onset of chronic cough; (b) forced expiratory volume in 1 second (FEV_1_) and forced vital capacity (FVC) ≥80% predicted or >lower limit of normal (LLN); (c) FEV_1_/FVC ≥0.7 or >LLN; (d) no evidence of asthma and (e) no regular symptoms of nasal/reflux disease.

Key exclusions include patients who (1) have previously tried low-dose morphine, pregabalin and/or a CCT with full intervention fidelity for the treatment of RCC/UCC; (2) are currently taking morphine or pregabalin for treatment of any indication (ie, RCC/UCC or chronic pain); (3) are currently taking other centrally-acting medication (ie, gabapentin, amitriptyline, dextromethorphan) for the treatment of any indication; (4) have a history of opioid or substance abuse; (5) are a current or ex-smoker with a >20 pack-year history or abstinence <6 months; (6) have cough due to angiotensin-converting enzyme inhibitor use; (7) have symptoms of an upper respiratory infection within the last month that have not resolved; (8) have had an asthma exacerbation within the last month that requires an increase or start of an oral corticosteroid; (9) have other primary pulmonary disorders, including pulmonary embolism, pulmonary hypertension, lung cancer, cystic fibrosis, radiologically proven emphysema, interstitial lung disease or severe bronchiectasis; (10) have creatinine clearance <15 mL/min, including individuals with end-stage renal disease who require haemodialysis or peritoneal dialysis; (11) have participated in another clinical trial of an investigational medicinal product within 30 days or (12) are pregnant or breastfeeding.

### Randomisation, allocation concealment and blinding

Authorised research staff will use an automated centralised randomisation system on Research Electronic Data Capture (REDCap) to ensure concealed allocation stratified by site and sex and with variable block sizes. The REDCap randomisation module will generate and conceal the allocation sequence, and research staff enrolling participants will not have access to the sequence prior to assignment. This is an open-label trial in which participants, study staff, investigators and treating clinicians will be aware of treatment assignment after allocation.

### Study interventions

#### Low-dose morphine

Patients will take oral morphine sulphate 5 mg two times per day until as tolerated or until the end of the study (1 year). Two trials suggest that this dose optimally balances efficacy and tolerability.^11
13^ It is also the lowest effective dose to mitigate the risk of dependency and addiction. Participants randomised to morphine will also receive a bowel regimen (polyethylene glycol 3350) to be taken as needed (PRN) for the prevention and management of constipation.

#### Pregabalin

Patients will orally titrate to their maximum tolerated dose up to 150 mg two times per day over 2 weeks using 25 or 50 mg tablets. Similar dosing occurred in a previous trial except their schedule involved quicker up-titration within 6 days.^8^ To mitigate adverse effects due to rapid up-titration, we will allow for a similar maximum tolerated dose, but with up-titration within 2 weeks. Renal-adjusted dosing will follow table 1 based on creatinine clearance.

**Table 1 T1:** Dosing schedule of pregabalin

Phase	Days	CLcr ≥60 mL/min	CLcr 30–60 mL/min	CLcr 15–30 mL/min
Titration	1–7	50 mg AM+50 mg PM	50 mg AM+50 mg PM	25 mg AM+25 mg PM
	8–14	100 mg AM+100 mg PM	100 mg AM+100 mg PM	50 mg AM+50 mg PM
Maintenance	15–21	150 mg AM+150 mg PM	150 mg AM+150 mg PM	75 mg AM+75 mg PM

CLcr, creatinine clearance estimated by the Cockcroft-Gault equation.

Patients will have a telephone visit at 2 weeks with their local study physician to determine their maintenance dose until the end of the study (1 year). If the patient requires stopping of pregabalin for any reason or they reach the end of the study, they should taper their dose over 2 weeks.

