### Sensitivity analyses

#### Testing the impact of protocol adherence

Anticipating that patients may discontinue treatment due to AEs, we will assess the robustness of the primary analysis at 6 weeks to deviations from the intervention protocol. This sensitivity analysis will occur with the primary outcome and select secondary outcomes in the per-protocol population.

For the morphine versus pregabalin comparison, the per-protocol population will include patients who received ≥80% of the intended study drug over the 6-week period. For the CCT versus no CCT comparison, the per-protocol population will include patients who (1) completed at least four out of the five weekly adherence diaries and (2) reported using at least one cough control strategy in three of those diary entries.

The same linear model or linear mixed-effects model described in the primary analysis will be applied to the per-protocol population.

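### Table 1's pregabalin schedule gives two different doses at a creatinine clearance of exactly 30 mL/min, and two of its three renal columns are identical without explanation

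*Protocol article*

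**What the plan says.** Under Study interventions, the Pregabalin section has patients titrate over 2 weeks to the highest dose they tolerate, capped at 150 mg twice daily. It adds: "Renal-adjusted dosing will follow table 1 based on creatinine clearance".

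Table 1 has three columns, headed "CLcr ≥60 mL/min", "CLcr 30–60 mL/min" and "CLcr 15–30 mL/min", with clearance estimated by Cockcroft-Gault. Its rows are two titration weeks (days 1–7 and 8–14) and a maintenance row labelled days 15–21. The paragraph below the table provides for a telephone visit at 2 weeks with the local study physician "to determine their maintenance dose until the end of the study (1 year".

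The Eligibility criteria exclude creatinine clearance below 15 mL/min, so the whole range covered by the table can be enrolled.

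**The concern.** The text presents Table 1 as the rule that turns a clearance value into a dose. Such a rule should give one dose for each value, and a reader expects a separate band to exist because something changes there. Table 1 fails the first test at one value. It also leaves the second unexplained for the middle band.

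Sites will dose from this table, so this is first a matter of participant safety and of uniform conduct across the five centres. Two sites could put a patient with the same clearance on schedules that differ by a factor of two, and both could point to the table. If the middle column was copied in error, every pregabalin patient in the 30–60 band would be affected, which is a wider group than those at exactly 30.

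**Working it through.** **Inputs.** All are from Table 1, with morning and evening doses added to give mg/day.

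| Days | ≥60 mL/min | 30–60 mL/min | 15–30 mL/min |
|---|---|---|---|
| 1–7 | 50 + 50 = 100 | 50 + 50 = 100 | 25 + 25 = 50 |
| 8–14 | 100 + 100 = 200 | 100 + 100 = 200 | 50 + 50 = 100 |
| Maintenance | 150 + 150 = 300 | 150 + 150 = 300 | 75 + 75 = 150 |

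**Step 1: shared boundaries.** The value 60 lies in the first and second columns, and the value 30 lies in the second and third. At 60 the two columns agree, so the overlap has no consequence. At 30 the ratios are 100/50, 200/100 and 300/150, which is 2 in every row.

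**Step 2: size over the randomised phase.** This assumes that the maintenance dose runs from day 15 to day 42 (28 days), as the paragraph under the table implies.

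- 30–60 column: 7 × 100 + 7 × 200 + 28 × 300 = 700 + 1,400 + 8,400 = 10,500 mg.
- 15–30 column: 7 × 50 + 7 × 100 + 28 × 150 = 350 + 700 + 4,200 = 5,250 mg.
- Ratio: 5,250 / 10,500 = 50%.

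**Step 3: identical columns.** The ≥60 and 30–60 columns match in 3 of 3 rows. Only the 15–30 column differs, at half the others throughout. In effect the table has two dose levels under three band headings.

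**Step 4: row label.** The maintenance row ends at day 21, while the text below continues maintenance to 1 year. The text settles what happens after day 21, so this is a labelling mismatch and not a gap in the schedule.

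**Step 5: reach into the statistics.** No stated sample size, power or alpha depends on Table 1.

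**The case against.** The best defence is that little is really in conflict. Clearance is a continuous estimate, and a value of exactly 30 will be uncommon. Two identical columns give one dose, not two, and both respect the 150 mg twice-daily ceiling in the text. The statement that dosing is renal-adjusted remains true, because the lowest band is halved. Much of this stands: the scheduled dose conflicts at one value only, and the identical columns may be deliberate. It does not remove the overlap at 30, and it does not explain why a separate 30–60 band is shown.

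A reader might also draw three stronger conclusions, which the document does not support.

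- *That sites have no dose after day 21.* The paragraph under the table has the maintenance dose set at the 2-week call and continued to 1 year.
- *That the morphine statements contradict each other.* The Abstract has "low-dose morphine (up to 5 mg two times per day" and the Low-dose morphine section has "Patients will take oral morphine sulphate 5 mg two times per day until as tolerated". Both give the same ceiling, the second is qualified by tolerability, and no consequence follows from the difference in wording.
- *That the table leaves the per-protocol rule without a denominator.* That rule admits "patients who received ≥80% of the intended study drug over the 6-week period". If intended meant the full table schedule, a patient who completed the titration and was then held at 100 mg twice daily would take 700 + 1,400 + 28 × 200 = 7,700 mg, or 73% of 10,500 mg, and would fail. At 75 mg twice daily from day 8 the figure is 700 + 7 × 150 + 28 × 150 = 5,950 mg, or 57%. The arithmetic is right, but the question arises from individual titration and not from the table's defects. The natural reading of intended is the dose set for that patient, on which both patients are at 100%. The rule serves only a sensitivity analysis, and its exact definition may sit in the statistical analysis plan, which is not shown.

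**Conclusion.** The point holds in a narrow form: Table 1 is internally inconsistent as a renal-adjusted schedule. At a clearance of exactly 30 mL/min it gives two doses that differ twofold in every row, 300 against 150 mg/day at maintenance. Over 6 weeks the totals are 10,500 and 5,250 mg if maintenance runs from day 15 to day 42. Separately, the ≥60 and 30–60 columns are the same throughout, and the document gives no means of telling a deliberate choice from a copying error. The label of the maintenance row is a minor mismatch with the text.

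How many participants this touches cannot be estimated, because the article gives no distribution of clearance. Intention-to-treat estimation, power and error control are unaffected. The reason to act is that sites dose from this table and that the correction is easy before the first patient is enrolled.

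**What to change.** Before enrolment, the sponsor should reconcile Table 1 with the text and with the source from which the schedule was taken:

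- Write the bands so that each clearance value falls in exactly one column.
- Confirm or correct the 30–60 column. If no adjustment is meant there, merge it with the ≥60 column; if the separate band is kept with the same doses, say that this is intended.
- Align the label of the maintenance row with the sentence that continues maintenance to 1 year.

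Which dose belongs in which band is for the sponsor to settle from that source; none is proposed here. The cost is a corrected table in a minor amendment, sent to sites before they start. No change to the sample size or to the analysis is needed.

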#### Cough control therapy

Patients assigned to CCT will attend five 45–60 min virtual sessions delivered by a trained physiotherapist or speech-language pathologist. The structure, based on prior literature^8
9
14^ and our group’s work,^17
18^ includes education, cough suppression strategies, breathing/laryngeal exercises and goal setting (table 2).

**Table 2 T2:** Summary of cough control therapy

Session	Week	Content
1	1	This session will focus on general education about chronic cough (ie, definitions, anatomy and mechanisms), introduction to cough suppression and goal setting. Participants will complete a baseline self-efficacy assessment using a combined measure consisting of the New General Self-Efficacy Scale^34^ and a brief, cough-specific self-efficacy scale developed for this study.^35^ Additionally, an entry interview will explore participants’ lived experiences with chronic cough and their expectations of the programme.
2	2	This session will focus on educating participants about cough triggers, behavioural sensitisation mechanisms and the benefits of non-pharmacological strategies. This session will also include the training and practice of 1–2 cough suppression techniques, with reinforcement of goal-oriented behaviour.
3	3	This session will cover the role of hydration, laryngeal hygiene and breathing exercises to control chronic cough.
4	4	This session will serve as a consolidation session, reviewing all aspects of cough control therapy and exploring the sustainability of the cough control strategies after the intervention.
5	6	This session will evaluate participants’ implementation of cough control strategies in daily life and their progress toward previously established goals. A final self-efficacy reassessment will be conducted, along with an exit interview to qualitatively explore participants’ experiences, barriers to maintenance and perceived impact of the therapy. Interview data will be analysed following a pre-specified protocol using reflexive thematic analysis.^36^

Participants will complete a weekly CCT diary asking them to reflect on the past 7 days and report: (a) how often they used cough control strategies (eg, urge suppression, breathing techniques); (b) in what contexts they applied these strategies (eg, at work, in public, while talking); (c) what barriers or facilitators influenced their ability to use the techniques and (d) the perceived effectiveness of the strategies scored on a 0–10 scale.

We will assess treatment fidelity and therapist adherence using a modified version of the Intervention Fidelity Monitoring Checklist for Trials in Chronic Cough.^22
23^ We will further evaluate participant engagement session-by-session through structured self-report checklists that assess perceived usefulness, understanding and confidence in applying each session’s content.^23^

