### Visit schedule

Trained research staff will perform all study visits. The study has in-person and telephone visits, with electronic administration of all patient-reported outcome measures on REDCap in English and French. Online supplemental file 4 provides a summary of the visits.

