#### Testing the effect of CCT on self-efficacy

Among participants receiving CCT, a linear model including fixed effects for site, time and baseline self-efficacy will assess changes on the New General Self-Efficacy Scale and the Cough Self-Efficacy Scale.

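### The final self-efficacy scales and the exit interview are tied to attending CCT session 5, so the exploratory self-efficacy change analysis and the exit-interview themes would cover session-5 attenders only

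*Protocol article*

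**What the plan says.** Table 2 sets out five CCT sessions. The first row holds the opening measures: "Participants will complete a baseline self-efficacy assessment using a combined measure consisting of the New General Self-Efficacy Scale" and a short cough-specific scale, and "an entry interview will explore participants’ lived experiences with chronic cough and their expectations of the programme". The last row, session 5 in week 6, holds the closing measures: "A final self-efficacy reassessment will be conducted, along with an exit interview to qualitatively explore" experiences, obstacles to keeping up the techniques, and perceived impact.

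The section Testing the effect of CCT on self-efficacy fits, among participants receiving CCT, a linear model that "will assess changes on the New General Self-Efficacy Scale and the Cough Self-Efficacy Scale". This model needs the closing score.

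The section Visit schedule says that research staff perform the study visits, "with electronic administration of all patient-reported outcome measures on REDCap in English and French". The measures described under Patient-reported outcome measures are the MCSQ, CS-VAS, LCQ, PGIC and PGIS, and EQ-5D-5L. The self-efficacy scales are not among them. The section Withdrawal of study participant encourages patients who stop treatment to keep attending follow-up visits for outcome data, but does not mention self-efficacy or the exit interview.

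**The concern.** Session 5 is a treatment session, not a study visit. A participant who gives up CCT after session 2 but comes to the week-6 assessment would supply cough outcomes there. On the text as it stands, that participant would supply no final self-efficacy score and no exit interview. Missing session 5 is plausibly related to what is being measured, since someone who found the techniques unhelpful has less reason to attend the last session.

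Two results are exposed: the mean change on the two self-efficacy scales, and the themes from the exit interview. The exit interview is the only end-of-programme qualitative source that the article describes. It matters because the Introduction says the trial will "assess its acceptability, the components that drive benefit, intervention fidelity and implementation considerations", and those who stopped are well placed to say why CCT did not suit them.

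**Working it through.** **Denominator.** The plan's own sample size reproduces. With d = 0.357/0.6 = 0.595, two-sided alpha 0.025 and 80% power, a two-sample t-test needs 54.97, so 55 per group. Then 55/(1 − 0.10) = 61.1, so 62 per group and 124 in total, as stated. Two of the four groups of 31 receive CCT: 2 × 31 = 62 assigned to CCT.

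**How many could be missing.** The documents give no rate of session attendance. The 10% dropout in the section Sample size is for the trial, so using it here is an assumption. Over an assumed range of 5% to 30%:

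- 5%: 62 × 0.05 = 3.1, about 3 participants
- 10%: 62 × 0.10 = 6.2, about 6
- 20%: 62 × 0.20 = 12.4, about 12
- 30%: 62 × 0.30 = 18.6, about 19

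**Size of the distortion.** Let m be the share missing session 5, A the mean gain in attenders and N the mean gain in non-attenders. The mean over everyone assigned to CCT is (1 − m)A + mN. The attender-only mean is A. The difference is A − [(1 − m)A + mN] = m(A − N). In SD units, with assumed gaps A − N:

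| Share missing | Gap 0.25 SD | Gap 0.5 SD | Gap 1.0 SD |
|---|---|---|---|
| 5% | 0.0125 | 0.025 | 0.05 |
| 10% | 0.025 | 0.05 | 0.10 |
| 20% | 0.05 | 0.10 | 0.20 |
| 30% | 0.075 | 0.15 | 0.30 |

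The sign follows the gap. If non-attenders gain as much as attenders, there is no bias; if they gain more, the attender-only mean is too low.

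**What depends on session 5 and what does not.**

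- Depends on it: change in the two self-efficacy scales, and the exit-interview themes.
- Does not: the moderator analysis by baseline self-efficacy, which uses the session 1 score and the 6-week outcomes; attendance, the weekly diaries, the session checklists and the entry interview; and the primary and secondary outcomes.

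**The case against.** A reader might infer that all acceptability results describe completers only. The article does not support that. The Discussion bases acceptability on utility scores, diaries, attendance and checklists as well as interviews. The weekly diary asks "what barriers or facilitators influenced their ability to use the techniques and (d) the perceived effectiveness of the strategies scored on a 0–10 scale". The section Cough control therapy adds: "We will further evaluate participant engagement session-by-session through structured self-report checklists that assess perceived usefulness, understanding and confidence". Attendance is counted, so stopping is itself recorded. The section Descriptive analyses at 6 and 12 months also documents why CCT participants do not continue the techniques. Early stoppers can contribute to all of these. Nor are session-5 attenders the same as completers: someone can miss earlier sessions and still come to the last.

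A reader might also infer that patients report the impact of CCT to the therapist who treated them. Therapists deliver the sessions, but the article does not say who conducts the interview, and it refers to a pre-specified protocol for the interview data that is not shown.

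It can further be said that the visit schedule is in a supplement that is not shown, so collection elsewhere cannot be excluded. That stands as a limit on certainty. It does not remove the point, because Table 2 positively places both measures in session 5.

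Finally, self-efficacy is neither a stated objective nor a listed outcome, and its change analysis is an uncontrolled before-after comparison within the CCT arm. It could not show a causal effect of CCT even with complete data. This stands, and it keeps the point minor.

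**Conclusion.** The point holds in a limited form. As written, the change analysis for self-efficacy and the exit-interview themes would cover session-5 attenders only, and the gain could be overstated if those who stop CCT gain less. The illustrative size is 0.05 SD at 10% missing and 0.15 SD at 30% missing. Both the attendance rates and the 0.5 SD gap are assumptions, and the direction is plausible but not shown.

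A larger relative figure is easy to produce and should not be used. If attenders gain 0.5 SD and non-attenders nothing, the mean over all is 0.5 × (1 − m) = 0.45, 0.40 or 0.35 at 10%, 20% or 30% missing, which gives ratios of 0.50/0.45 = 1.11, 0.50/0.40 = 1.25 and 0.50/0.35 = 1.43. Those ratios follow entirely from the assumed zero gain, for which the documents give no basis.

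Severity is minor. The primary outcome, the secondary outcomes and the sample size are untouched.

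**What to change.** Administer the final self-efficacy scales by REDCap at the existing week-6 assessment to every participant assigned to CCT, whether or not they attended session 5, and run the change analysis on all of them. Because the opening score is taken in session 1, say how anyone who never attended that session enters the model.

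Where feasible, offer the exit interview to participants who stopped CCT as well. Where it is not, report the interview findings as describing session-5 attenders. Moving every interview to research staff is a resource choice that this point does not require.

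If the visit schedule already collects the scales at week 6 from all CCT participants, a sentence in Table 2 saying so is enough. Otherwise the cost is one short electronic form at a planned visit, plus some staff time for any added interviews.
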